## Methods

### Study Design

This study, called YumABLE, started in June 2024, when recruitment began, and is anticipated to end by fall 2025. The study is a 3-arm randomized controlled trial for evaluating the delivery of a 6-month intervention, which involves telecoaching, diabetes educational content, and technology access, to 90 individuals with diabetes and physical disabilities. The 3 intervention groups are a high-technology group, a low-technology group, and an attention control group. Study participants are adults aged 18 to 65 years with a permanent disability and T2D. All study groups receive an initial 60-minute 1:1 assessment, 4-weekly remote DSME classes, a make-up class option, and a follow-up class 3 months after the last DSME class. Each of the weekly remote classes as well as the follow-up classes are 90 minutes in length. The 3-month follow-up remote class is 60 minutes in length. DSME classes are organized into cohorts, with each cohort consisting of up to 10 participants. DSME classes and education will be of the same quality and quantity for all participants regardless of study group.

The difference among study groups is that the high-technology intervention group receives weekly diabetes-related materials delivered through multiple modalities (email, text, and telehealth platform), regular text reminders (to read the material, track health data, motivation, etc), and bidirectional SMS text messaging to enable timely communications with the certified diabetes care and education specialist (CDCES). Participants also have access to the telehealth platform. The low-technology intervention group receives 1 weekly email containing diabetes-related materials and bidirectional email communication with the CDCES. It does not have access to the telehealth platform. The attention control group, the “no technology” group, is only provided with DSME classes and has no technology support. It is not provided with any additional related content or access to technology-based support resources. Outcome measures are assessed at baseline and 6 months (Figure 1), with data collected from all intervention groups. Four weeks is considered a month in this study, making the study duration 24 weeks. Study activities are primarily conducted on the web nationally in the United States.

**Figure 1 figure1:**
[figure not shown]
Flowchart of the protocol.

### Study Population

The American Diabetes Association defines a diagnosis of T2D as an HbA_1c_ level of 6.5% or higher, reflecting average blood glucose levels over the past 2 to 3 months. Likewise, the National Health and Nutrition Examination Survey’s Physical Functioning Survey will be used to identify permanent physical impairments. The participants consist of adults aged 18 to 65 years.

### Inclusion Criteria

Eligible participants must meet the following inclusion criteria: (1) have been diagnosed with T2D; (2) be aged 18 to 65 years; (3) be living with a permanent physical disability such as spinal cord injury, spina bifida, multiple sclerosis, or stroke; (4) have the ability to converse in and read English; (5) have a smartphone or computer available that can run apps; and (6) have Internet connection capabilities.

### Exclusion Criteria

Exclusion criteria were (1) current enrollment in any diabetes-related intervention, (2) a present or soon-planned pregnancy, (3) a major heart attack or heart surgery in the past 12 months, and (4) having undergone dialysis, kidney transplant, or a kidney surgery in the past 12 months.

### Recruitment

Participants are recruited digitally from the United States. Information about the study is shared through the National Center on Health, Physical Activity and Disability website and their affiliated social media outlets. Participants are additionally recruited from a database containing information on previous diabetes research studies with similar inclusion criteria. Emails are sent to these potential participants, providing details about the YumABLE program, and including a link for them to complete the study screening process and consent if they are eligible. During the screening process, participants are asked to self-report their HbA_1c_ levels to confirm their diabetes status. While many reported HbA_1c_ levels consistent with a diabetes diagnosis, baseline HbA_1c_ testing conducted by a contracted third party showed that some participants had lower levels, indicating prediabetes or normal glycemic status. These individuals were not excluded from the study, as it is possible that their HbA_1c_ levels had decreased since their previously reported values. Additionally, some participants, due to mobility challenges or limited access to the contracted laboratory, could not complete their baseline HbA_1c_ test. We accepted these individuals’ self-reported HbA_1c_ levels as measured during recent visits to their health care provider (within 3 months of enrollment in the study). Eligible participants who pass the screening process must sign an informed consent form and complete baseline surveys.

Upon enrollment in the study, participants receive an automated email containing a HIPAA (Health Insurance Portability and Accountability Act)-compliant REDCap (Research Electronic Data Capture) link to access a survey packet. REDCap is a secure program developed collaboratively by Vanderbilt University and the National Institutes of Health National Center for Research Resources [36]. A total of 28 participants have been recruited. The survey packet includes a demographic survey and primary outcome measures detailed in Table 1.

**Table 1 table1:** Outcome measures and assessment timeline.

Variable		Instrument	Time point

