### Randomization

After completing baseline surveys, participants are randomly assigned to 1 of 3 groups: the high-technology, low-technology, or attention control groups. The randomization sequence was created and stored in REDCap, automatically assigning participants to their respective groups with a 1:1:1 allocation ratio. The random allocation sequence was generated by study personnel using REDCap. Trained study staff enrolled participants and assigned them to intervention groups through the REDCap randomization module, which concealed the allocation sequence until assignment.

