#### Secondary Outcome Measure: HbA1c Levels

HbA_1c_ is measured using an HbA_1c_ test. HbA_1c_ results are transmitted from the testing company to study personnel and inputted directly into REDCap. Similarly, if participants self-report their HbA_1c_ results, study personnel will input them directly into REDCap. HbA_1c_ is measured both at baseline and at 6 months. The HbA_1c_ is a widely recognized test to assess the effectiveness of diabetes management strategies.

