Given that self-management is crucial in managing T2D and also considering that persons with disabilities face barriers that prevent them from successfully managing their diabetes, a study looking to create an available, inclusive, and accessible diabetes management program for people with disabilities is important. To the best of our knowledge, there is no existing program in the United States explicitly providing remote DSME and MNT tailored for persons living with disabilities.

This study has limitations. Factors such as the supportive group setting, the instructor, or individual components of the program may influence health outcomes in different ways. To account for potential confounding factors, we have chosen a randomized design. Additionally, behavior changes, such as participating in an organized intervention, could contribute to improvements, including adopting healthier diets. As with any complex intervention, various factors may impact the outcomes. However, this reflects real-world clinical scenarios. Using a randomized design, the study aims to minimize the influence of confounding variables and provide more reliable findings. Additionally, several aspects of our trial design may pose potential limitations. First, participants with mobility limitations or accessibility issues may be unable to visit the contracted laboratory for their HbA_1c_ test and instead self-report their HbA_1c_ levels. These self-reported data may not be entirely accurate or up to date. Additionally, as the study is conducted remotely, some participants, particularly older individuals, may face technical challenges, such as difficulty navigating the platform or accessing the intervention materials.

That notwithstanding, this study has some strengths. To begin with, the methodological strengths of the study include the randomized controlled design, preregistration in a clinical trials registry, the inclusion of make-up and follow-up classes, and the use of both quantitative and qualitative measures. Another strength is a third-party testing company’s involvement in the HbA_1c_ tests, ensuring impartiality and reliability in the results.

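### HbA1c mixes laboratory and self-reported values with no rule for handling source, so change can partly reflect a change of source; separately, the baseline draw is not required to precede randomisation

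*Protocol article*

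**What the plan says.** HbA1c is the only secondary outcome (Table 1) and is named in the hypotheses in the Introduction and Results. Under Secondary Outcome Measure, "HbA_1c_ is measured both at baseline and at 6 months".

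**Source.** Recruitment explains that some participants, "due to mobility challenges or limited access to the contracted laboratory, could not complete their baseline HbA_1c_ test". For them the study took "self-reported HbA_1c_ levels as measured during recent visits to their health care provider (within 3 months of enrollment in the study"). Secondary Outcome Measure adds that "if participants self-report their HbA_1c_ results, study personnel will input them directly into REDCap", and the Outcomes overview repeats this; neither names a visit.

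**Disagreement between sources.** Recruitment says many participants reported levels consistent with diabetes at screening, whereas "baseline HbA_1c_ testing conducted by a contracted third party showed that some participants had lower levels, indicating prediabetes or normal glycemic status". It continues: "These individuals were not excluded from the study, as it is possible that their HbA_1c_ levels had decreased since their previously reported values".

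**Timing.** Under Randomization, "After completing baseline surveys, participants are randomly assigned to 1 of 3 groups". The text after Table 1 says that a welcome call follows the survey packet within a week, and that the laboratory requisition then comes by post within another week.

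**Analysis.** Statistical Analysis plans paired t tests of change within each arm and mixed models under intention-to-treat. Source is not mentioned. The Discussion admits that self-reports may be inaccurate or out of date, and separately credits third-party testing with "ensuring impartiality and reliability in the results".

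**The concern.** A change score assumes that the same quantity was measured the same way twice. Here one visit may supply a laboratory result and the other a figure that the participant recalls from a provider visit. If the two sources differ systematically, the difference enters the change as though it were a response to the programme. The article has itself seen laboratory results in a lower glycaemic category than many self-reports would suggest. Its explanation, a true fall since the earlier value, does not remove the problem: if levels had moved between report and test, an older report is a poor baseline for a 6-month change.

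The stake is highest for the within-arm paired tests, because they have no control arm against which a shared artefact cancels.

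The timing question is a different one. A baseline drawn after allocation could be influenced by knowledge of the arm or by the first contacts of the programme. It does not cause source switching.

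**Working it through.** **Inputs from the article.** 30 per arm, two-sided 0.05, ANCOVA, baseline-to-follow-up correlation r = 0.7, effect size 0.65, power 80% (Sample Size); loss to follow-up about 20% (Statistical Analysis), so 30 × 0.8 = 24 completers per arm. It gives no number of self-reports, switching share, source difference or HbA1c SD.

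**The article's own figure.** ANCOVA residual SD = √(1 − 0.7²) = 0.714. A plain two-arm comparison at effect 0.65 has 94% power with 30 per arm and 88% with 24. About 80% is reached with 24 completers per arm, either by a three-arm F test with equally spaced means (79.4%) or by two comparisons at alpha 0.025 (81.9% normal, 79.5% t). The article does not say which was used, and this point does not depend on it. The design values serve only as a yardstick.

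**Assumptions below.** Self-report exceeds laboratory by b HbA1c points; SD of HbA1c is 1.5 points; r = 0.7 applies to HbA1c. Switching in the opposite direction reverses the sign, so p is the net share moving from self-report to laboratory.

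**1. Within-arm change.** Shift = p × b.
- p = 10%, b = 0.2: 0.02 points
- p = 30%, b = 0.5: 0.15 points
- p = 30%, b = 1.0: 0.30 points

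SD of change = 1.5 × √(2 × (1 − 0.7)) = 1.16; with 24 completers SE = 1.16/√24 = 0.24. A shift of 0.15 points is 0.63 SE and gives a paired test about a 10% chance of significance (normal approximation) with no true change. A shift of 0.30 points is 1.26 SE and gives about 24%; 0.02 points leaves it at about 5%.

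**2. Between arms.** Bias = (difference in net switching share) × b. With equal expected switching this is zero.
- Difference 10 percentage points, b = 0.5: 0.05 points = 0.05/1.5 = 0.03 SD, 5% of the 0.65 design effect. SE = 0.714 × √(2/24) = 0.206 SD; type I error about 5.3%.
- Difference 30 percentage points, b = 1.0: 0.30 points = 0.20 SD, 31% of 0.65; type I error about 16%.

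**3. Noise alone.** Suppose a share q of values at each visit carries independent self-report error of SD e. Variance becomes 1.5² + q·e² and the correlation 0.7 × 1.5²/(1.5² + q·e²).
- q = 10%, e = 0.5: correlation 0.69; two-arm power at 24 per arm falls from 88% to 87%.
- q = 30%, e = 1.0: correlation 0.62; power falls to 77%.

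**4. Smaller numbers.** Recruitment and Results report 28 participants, while the Abstract reports 90. At about 9 per arm the between-arm SE is 0.714 × √(2/9) × 1.5 = 0.50 points, so a 0.05–0.30 point bias is 0.10–0.59 SE and type I error about 5.1–9%. A fixed artefact then distorts the test less, because the estimate is already so imprecise.

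**5. Timing.** Set side by side, the only stated trigger for allocation is survey completion, while the requisition may arrive up to about two weeks after the survey packet (a week to the call, a week for the post). A participant who completes the surveys promptly can be allocated before being tested. The text neither requires nor reports this.

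**The case against.** The strongest reply is that little of this is documented as having happened. The only recorded use of self-report is at baseline. The stated cause, mobility or laboratory access, may persist, so the same person may self-report twice and never switch. The welcome call announces the requisition and speaks of randomisation as still to come, which fits testing first, and the flowchart is not available. HbA1c reflects 2 to 3 months by the article's own account (Study Population), so a draw shortly after allocation would move little. The limitation is disclosed, and source covariates normally belong in an analysis plan. Much of this stands, and it limits the wording to what the rules permit. It does not remove the point: the data rule is stated in the article, and neither a source requirement nor a pre-allocation test goes with it.

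Several stronger readings are tempting but unsupported.
- A reader might infer that self-reports are selected to be high, so that a self-reported baseline followed by a laboratory value must show a fall. Self-reported HbA1c was used at screening to confirm diabetes status, but the inclusion criterion is a diagnosis with no HbA1c cut-off. Only many, not all, reported diabetic levels, and the article says nothing about laboratory values that came out higher. Nor does it say that the accepted baseline is the screening figure.
- A reader might treat chance imbalance in source between small arms as bias. Under randomisation it is random error, which the standard error covers.
- A reader might call retention of participants below 6.5% an error. It fits the diagnosis criterion and intention-to-treat.
- A reader might see a contradiction in the Discussion. The sentence on reliability concerns the third-party tests, so it does not conflict with the caveat on self-reports.

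**Conclusion.** The concern holds in limited form. Mixing of sources at baseline is explicit; mixing at 6 months is permitted. HbA1c change can therefore partly measure a change of source, chiefly in the within-arm paired tests, with added noise elsewhere. Bias in the arm contrast needs switching that differs by arm. That is conceivable, since the arms differ in contact and health tracking, but it is not shown. A baseline draw after allocation is a separate weakness, permitted but not shown.

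The documents do not allow the size to be derived. Under the stated assumptions it runs from negligible (0.02 points within arm; type I error 5.3% between arms at 24 per arm) to material (0.30 points; 16%). The upper ends need 30% net switching, or a 30-point difference between arms, together with a full 1.0-point difference between sources. No change in sample size follows.

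**What to change.** 1. Record source (laboratory or self-report) and draw date for every HbA1c value, and report both by arm and visit. Laboratory results are transmitted by the testing company and self-reports are entered by staff, so source should be recoverable.
2. Keep all participants in the main baseline-adjusted intention-to-treat analysis. Baseline source may be added as a covariate. Follow-up source should not be, because it arises after randomisation and adjusting for it can introduce bias if the arm affects it.
3. Prespecify, while the statistician is still blinded, one sensitivity analysis restricted to laboratory values at both visits with the baseline drawn before the first class.
4. Report HbA1c conclusions alongside that analysis, without making it a pass-or-fail gate: it rests on a smaller, selected subset. Do not interpret within-arm change from mixed-source pairs as a treatment effect.

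The cost is two data fields and one extra analysis. The downside is wider intervals in the laboratory-only analysis.

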**Primary outcome measures**			
	Diabetes quality of life	Diabetes Quality of Life Measure	Baseline, postintervention
	Psychological distress	Diabetes Distress Scale	Baseline, postintervention
	Self-efficacy	Diabetes Empowerment Scale	Baseline, postintervention
**Secondary outcome measure**			
	Glycemic management	HbA_1c_^a^	Baseline, postintervention
**Other prespecified outcome measures**			
	Physical activity	Godin Leisure-Time Exercise Questionnaire	Baseline, postintervention
	Dietary intake	The UK Diabetes and Diet Questionnaire	Baseline, postintervention
	Medication adherence	Medication Adherence Rating Scale	Baseline, postintervention
	Health dashboard usability	System Usability Scale	Baseline, postintervention

^a^HbA_1c_: glycated hemoglobin.

After participants receive the initial survey packet, a member of the research team calls the participants within a week. The purpose of this call is to welcome participants into the study and go over study components. During the call, the research personnel informed participants that they will receive a laboratory requisition in their mail within a week, allowing them to visit a third-party clinical testing company location to have their blood glucose tested at no cost. The research staff also lets participants know that they will be randomized into 1 of the 3 intervention groups. Participants were not informed about which intervention was the primary focus or “intervention of interest” versus the comparator groups.

### Randomization

After completing baseline surveys, participants are randomly assigned to 1 of 3 groups: the high-technology, low-technology, or attention control groups. The randomization sequence was created and stored in REDCap, automatically assigning participants to their respective groups with a 1:1:1 allocation ratio. The random allocation sequence was generated by study personnel using REDCap. Trained study staff enrolled participants and assigned them to intervention groups through the REDCap randomization module, which concealed the allocation sequence until assignment.

### Sample Size

In total, 90 participants will be enrolled, divided into 3 groups of 30 participants each (low-technology, high-technology, and attention control). The sample size is determined based on the primary use of analysis of covariance and uses a 2-sided test with a type I error rate of 0.05. An intention-to-treat analysis and multiple imputations are incorporated. Given a minimum correlation of 0.7 between the baseline and follow-up outcomes, there will be an 80% chance of detecting an effect size of 0.65.

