**Results:**

Data collection began in June 2024 with a total of 90 recruited participants. The intervention was delivered. Make-up classes were delivered to participants in any of the 3 cohorts between November 2024 and December 2024. The final 3-month follow-up classes were held for each cohort 3 months after the first class. Data analysis is anticipated to be completed in fall 2025.

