## Results

We hypothesize that participants in the high- or low-technology intervention groups will show improvements in self-management behaviors related to T2D and self-efficacy compared to the control group at the 6-month follow-up. Again, we hypothesize that the high-technology intervention arm will result in better outcomes regarding reductions in HbA_1c_ than the low-technology and control arms. Additionally, we also hypothesize that the YumABLE intervention is feasible and acceptable to adults with permanent physical disability and T2D and that fidelity to the program will be maintained.

The development of the telehealth platform, which includes the dashboard and educational content, along with the creation of the landing website, has been completed by the study’s technical support team. In addition, research personnel have developed the database using REDCap to serve as the storage for data and communication tools such as emails and text notifications. The study began in June 2024. Since June 2024, intervention materials have been finalized, the IRB submissions have been completed, and participant recruitment began. In total, 28 participants have been enrolled and received the MNT and DSME remote class. Recruitment has ended, and we anticipate completing data collection by August 2025. Make-up classes were delivered to participants in any of the 3 cohorts between November 2024 and December 2024. The final 3-month follow-up classes were held for each cohort 3 months after the first class and were completed in February 2025. Data will be analyzed in fall 2025. Manuscript preparation and dissemination of study results are planned for spring 2026.

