The results from this study will expand our understanding of how technology-delivered behavioral interventions can effectively address the challenges of managing diabetes, particularly among individuals with permanent physical disabilities and their families. A combined approach of DSME and technology offers a promising, easily accessible, and engaging intervention that may serve as a practical pathway for improving diabetes management.

This study provides future directions. First, it can lead to more studies on how artificial intelligence could be used in the delivery of diabetes education among individuals with various forms of disabilities. In addition, the study can help provide insight regarding an effective approach to combine more than 1 technology in providing diabetes management education.

We intend to present study findings at diabetes, endocrinology, and digital health conferences and submit the data for publication in peer-reviewed open-access publications. In addition, we will consult with health care leaders and diabetes care teams within our health system on potential changes to diabetes education methods and digital intervention protocols.

In conclusion, this randomized controlled study, with an anticipated 90 participants, will explore the effects of combined DSME and technology among individuals with diabetes and a permanent physical disability. The primary aim is to assess how technology-enhanced DSME influences diabetes management. The findings from this intervention study could offer valuable insights for health care professionals, health educators, and public health personnel, informing future strategies for managing diabetes in individuals with physical disabilities and more broadly among all persons living with T2D.

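### The article reports both 90 and 28 participants recruited; if 28 is correct, the stated 80% power does not describe this trial

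*Protocol article*

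**What the plan says.** Sample Size sets the target: "In total, 90 participants will be enrolled, divided into 3 groups of 30 participants each". It bases the calculation on analysis of covariance, a two-sided 5% test and a baseline to follow-up correlation of at least 0.7, and concludes that "there will be an 80% chance of detecting an effect size of 0.65". Neither the units of 0.65 nor the contrast is given. Statistical Analysis anticipates about 20% loss to follow-up.

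Four places speak to the number enrolled:
- Abstract, Results: "Data collection began in June 2024 with a total of 90 recruited participants".
- Recruitment: "A total of 28 participants have been recruited".
- Results: "In total, 28 participants have been enrolled and received the MNT and DSME remote class", and in the same paragraph "Recruitment has ended, and we anticipate completing data collection by August 2025".
- Discussion, closing paragraph: "this randomized controlled study, with an anticipated 90 participants".

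Two further statements bear on which figure is right. Study Design describes the classes as run in cohorts, "with each cohort consisting of up to 10 participants". The Abstract and the Results section both refer to three cohorts, and Results says that their 3-month follow-up classes were completed in February 2025.

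**The concern.** The Abstract's 90 and the Results section's 28 are both given as actual counts, and they differ by a factor of about three. An interim count does not explain the difference, because Results closes recruitment in the paragraph that gives 28.

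The power statement depends on which figure is true. The article hypothesises that the high-technology arm will do better than the other two on self-management and HbA1c. A reader who takes 90 participants and 80% power from the Abstract and Sample Size would see a null comparison as fairly informative. With 9 or 10 people per arm it would say little. Analysis is scheduled for fall 2025, so the wording can be settled before results are read.

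**Working it through.** **Which count the text supports.** Three cohorts × at most 10 = at most 30 people. That accommodates 28. Ninety people would need at least 90/10 = 9 cohorts.

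**Inputs.** From Sample Size: 30 per arm, correlation 0.7, two-sided 0.05, effect 0.65, power 80%. From Randomization: 1:1:1 allocation. From Statistical Analysis: 20% loss. Assumption: 0.65 is a difference in outcome SD units. Residual variance after baseline adjustment is 1 − 0.7² = 0.51. Per-arm numbers at 28 are 28/3 = 9.33, and after 20% loss 22.4/3 = 7.47.

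**Pairwise ANCOVA.** SE = √(0.51 × 2/n), noncentrality = 0.65/SE, t test on 3n − 4 degrees of freedom.

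| n per arm | SE | Noncentrality | Power | Difference with 80% power | 95% CI half-width |
|---|---|---|---|---|---|
| 30 | 0.184 | 3.53 | 94% | 0.52 | 0.37 |
| 24 (30 less 20%) | 0.206 | 3.15 | 87% | 0.59 | 0.41 |
| 9.33 | 0.331 | 1.97 | 47% | 0.97 | 0.68 |
| 7.47 | 0.370 | 1.76 | 38% | 1.09 | 0.78 |

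This formula does not reproduce the plan's 80%. It gives 94% at 90 participants, and 87% after loss. The plan's figure is therefore conservative on this reading, and 47% must not be set against 80% as if both came from one calculation.

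**Omnibus F test, three arms, middle arm halfway.** Means 0, 0.325 and 0.65; noncentrality = n × 0.21125/0.51; F on 2 and 3n − 4 degrees of freedom. Power is 88% at 30 per arm, 79% at 24, 36% at 9.33 and 29% at 7.47. The 79% comes close to the stated 80%, but the article does not say that this test, or an allowance for loss, was used.

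**Scaling from the plan's own 80%.** If 90 participants give 80%, the standardised signal is 1.96 + 0.84 = 2.80. At 28 it is 2.80 × √(28/90) = 1.56, and power is Φ(1.56 − 1.96) = Φ(−0.40), about 35%. At 22.4 it is 2.80 × √(22.4/90) = 1.40, and Φ(−0.56) is about 29%. If the stated 80% already allowed for the loss, the figure stays at about 35%.

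**Range.** About 35% to 47% at 28, and about 29% to 38% after 20% loss.

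**The case against.** The strongest reply is that Sample Size is a prospective statement of a target, and a later shortfall does not make it wrong. That stands: the defect is the conflict over enrolment, together with a power statement left unqualified beside a count of 28. If 90 is correct, the power concern disappears.

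A reader might infer three stronger things that the article does not support.
- That enrolment of 28 is established. The cohort arithmetic favours it, but the Abstract mentions three cohorts in the same paragraph as 90 recruited, so only the investigators can settle it.
- That power has fallen from 80% to 47%. The pairwise formula behind 47% gives 94% at 90, so the two figures are on different footings, and 47% is near the favourable end of the range.
- That a confirmatory trial will almost certainly be non-significant. The title calls the trial pilot and feasibility, Data Management calls it a pilot feasibility and efficacy study, and nowhere is it called confirmatory. At 47% power a true effect of 0.65 is missed about 53% of the time, and at 38% about 62%: more likely than not, but not near certainty.

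The choice of contrast also matters. One hypothesis in Results sets the high- or low-technology groups against control. If that means pooling the two technology arms, a normal approximation gives about 62% power at 28 and 53% after loss, still short of 80%. Without baseline adjustment, pairwise power at 28 would be only about 26% to 29%.

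**Conclusion.** The contradiction is certain and needs no assumption: the article gives two incompatible totals. The consequence for power is conditional on 28 being correct. It also rests on reading 0.65 as a difference in SD units, a correlation of 0.7, a two-sided 5% test, and a pairwise or three-arm omnibus comparison. On that basis the trial falls well short of 80%, and an interval for any pairwise difference would extend further on each side than the effect it was sized to detect. A single replacement power figure is not warranted, because the article does not say which contrast produced its 80%.

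**What to change.** Reconcile the count in the Abstract, Recruitment, Sample Size, Results and the closing paragraph of the Discussion. If 90 is correct, correct the two statements of 28 and the cohort description.

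If 28 is correct, amend Sample Size to:
- state that the target was 90 and that 28 were enrolled;
- name the contrast and the units of 0.65, and recompute power by the method that gave 80%, or else give the ranges above with their assumptions;
- give the pairwise difference detectable with 80% power, about 1.0 SD at 28 and about 1.1 SD after 20% loss;
- state that between-arm efficacy contrasts will be reported as estimates with 95% confidence intervals, and that a non-significant result is not evidence of no effect.

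This is a change of text and reporting rules and needs no new data. The cost is a less favourable stated power and a more modest efficacy claim.
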